### Recruitment {20}

Recruitment will be done through village-level sensitization. Eligible households will be listed, and one woman randomly selected per household. Block randomization will ensure group balance.

### Randomization and allocation

#### Sequence generation {21a}

Participants will be randomly assigned to either the intervention or control group using a block randomization approach to ensure balanced allocation. Randomization will be conducted in small, variable block sizes (e.g., blocks of 4), with possible sequences such as ABAB, BABA, AABB, or BBAA (where A = intervention, B = control). A pre-generated randomization list will be prepared by an independent statistician to guarantee equal group sizes and minimize allocation bias.

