### Participant timeline {18}

#### Sample size {19}

The sample size was calculated based on hemoglobin (Hb) as the key outcome variable. Considering a standard deviation (SD) of 1.2 g/dL and a minimum detectable difference (Δ) of 0.5 g/dL between the intervention and control groups, the required sample size was estimated to provide 80% power (*β* = 0.20) at a two-sided significance level of 5% (*α* = 0.05, 95% confidence level). The sample size was adjusted accordingly to account for an anticipated 10% attrition due to loss to follow-up, pregnancy, or withdrawal. The final required sample size is 202 participants, with 101 participants allocated to the intervention group and 101 participants to the control group [18, 19]. Since we will pool the data from two sites for the main outcome measures, the total sample size will be equally divided into two study sites.

The sampling strategy for this study involves a multi-stage approach to ensure methodological rigor and reduce potential biases. Initially, eligible villages will be purposefully selected from study areas based on predefined inclusion criteria such as population size, accessibility, and anemia prevalence data, if available. Within each selected village, a household listing will be conducted to identify households with at least one eligible non-pregnant, non-lactating (NPNL) woman of reproductive age. In instances where more than one eligible woman resides in a single household, one participant will be selected using simple random selection methods—such as a coin toss or random number generation—to prevent intra-household clustering and to maintain the independence of observations. This ensures that each household contributes only one participant to the study. Following this, the identified households will be subjected to block randomization, as previously described, to assign participants into intervention and control groups in balanced proportions. This sampling framework enables equitable group allocation, reduces selection bias, and ensures that the study sample is representative of the target population within the selected geographic context.

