### Type of randomization {21b}

Restricted randomization (block randomization) with a 1:1 allocation ratio will be used. The block size and sequence order will remain concealed from the field team to prevent predictability.

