### Allocation concealment mechanism {22}

Allocation will be concealed using sequentially numbered, opaque, sealed envelopes (SNOSE), managed exclusively by the independent statistician. Each envelope will contain the allocation code and will be opened only after eligibility confirmation and participant consent.

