### How blinding will be achieved {24b}

To maintain blinding, all blood samples will be labelled with anonymized study codes rather than allocation labels. Therefore, the laboratory staff will be unaware of the participants’ group assignments. Similarly, the trial statistician will receive only coded datasets where groups are labelled “Group A” and “Group B.” The cookware used in the intervention arm differed visibly from the control cookware (iron vs. non-iron); hence, participant blinding was not feasible.

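### The published A/B arm key matches the analyst's group labels, the example block scheme undercuts the promised concealment, and neither randomisation nor the stated models name site

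*Protocol article*

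**What the plan says.** All references are to the protocol article.

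- **Sequence generation {21a}:** "Randomization will be conducted in small, variable block sizes (e.g., blocks of 4), with possible sequences such as ABAB, BABA, AABB, or BBAA". The same sentence gives the key to the letters: "where A = intervention, B = control".
- **Type of randomization {21b}:** "The block size and sequence order will remain concealed from the field team to prevent predictability". Allocation is 1:1 in blocks, and no stratification factor is given.
- **Allocation concealment mechanism {22}:** "Allocation will be concealed using sequentially numbered, opaque, sealed envelopes (SNOSE), managed exclusively by the independent statistician". They are opened only once eligibility and consent are settled.
- **Who will be blinded {24a}:** participants and the field investigators who deliver the intervention are unblinded. Laboratory staff and analysts are to be blinded, the analysts by working on data stripped of group identifiers.
- **How blinding will be achieved {24b}:** "the trial statistician will receive only coded datasets where groups are labelled" Group A and Group B.
- **Sample size {19}:** data from the two sites are pooled for the main outcomes, and "the total sample size will be equally divided into two study sites".
- **Primary and secondary outcomes {27a}:** the mixed models contain arm, time and their interaction, with random effects for participants and, where relevant, clusters.
- **Additional analyses {27d}:** the adjustment covariates are age, BMI, starting iron status, diet, CRP and socioeconomic status. Site is named in neither section.

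**The concern.** There are three separate weaknesses.

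**Analyst blinding.** The code that is meant to hide the arm from the statistician uses the same two letters that the article has decoded in print. No section says that the dataset letters are reassigned. Anyone who has read the protocol could then identify the arms while modelling choices, exclusions and sensitivity analyses are still open.

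**Concealment of the block scheme.** The article appeared on 31 October 2025 and recruitment starts in December 2025. Field staff can therefore read an example block size and example sequences that {21b} says they will not know. They also see which households have already received iron cookware. Sealed envelopes hide the next allocation physically but do not prevent inference from past ones. Enrolment involves some judgement, since women must be willing to cook regularly and use the iron utensils supplied, and field investigators enrol. Foreknowledge could therefore influence who enters, and selection of that kind cannot be undone in the analysis.

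**Site.** Study setting {13} describes the two districts as varying in diet, socioeconomic conditions and access to care, and hopes to compare effectiveness between settings. Nothing stated secures arm balance within a district or removes district differences from the error term.

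**Working it through.** **The plan's own figure.** {19} gives SD 1.2 g/dL, difference 0.5 g/dL, two-sided alpha 0.05, 80% power and 10% attrition. Per arm, n = 2 × [1.2 × (1.960 + 0.842) / 0.5]² = 90.4. Dividing by 0.9 gives 100.5, so 101 per arm and 202 in total. The figure reproduces and nothing below changes it. Two equal sites means 101 women per site. The article gives no figure for predictability or for balance within site.

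**Analyst labels.** No arithmetic applies. {21a} sets A to intervention and B to control; {24a} says identifiers are removed; {24b} supplies groups called A and B. These fit together only if the dataset letters are reassigned, which is not stated.

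**Predictability.** Assume equally likely sequences, a known block start and all earlier allocations seen.

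- *Only the four listed sequences, size fixed at 4.* After AB the block must continue AB; after BA, BA; after AA, BB; after BB, AA. Positions 3 and 4 are always fixed: 4 sequences × 2 positions = 8 of 16 = 50% certain.
- *All six balanced sequences (adding ABBA and BAAB), size fixed at 4.* Position 4 is always fixed (6 cases) and position 3 is fixed after AA or BB (2 cases): 8 of 24 = 33% certain.
- *Sizes 4 and 6 mixed at random, all permutations* (sizes assumed; simulated for 101 participants, with the guesser knowing the two sizes but not which is in use): about 6% certain.

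| Scheme | Certain | Average success of best guess |
|---|---|---|
| Four listed sequences, size 4 | 50% | 75% |
| All six sequences, size 4 | 33% | 71% |
| Sizes 4 and 6 mixed | about 6% | about 69% |

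Mixing sizes removes most of the certainty. The average best guess falls much less, because this guesser still sees every past allocation and knows the possible sizes. That is a reason not to publish the sizes.

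**Balance within site.** Assume one list of 202 serves both sites and each woman is equally likely to come from either. Within a balanced block of 4, the arm difference among women from one site has variance 4 × ¼ = 1. Over 202/4 = 50.5 blocks the variance is 50.5 and the SD is √50.5 = 7.1 women. A simulation with exactly 101 women per site agrees: mean absolute difference about 6, 95th percentile 13. If each site instead used a consecutive run of 101 envelopes, the simulated difference was 1.

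**The case against.** The strongest reply concerns the block scheme. A reader might infer that only four sequences will be used and that half of all allocations are predictable. The text does not support that. It says the block sizes vary, and it introduces both the size of 4 and the four sequences as examples. The 50% figure requires a fixed size of 4, an exhaustive list of four, a known block start and sight of every earlier allocation. This stands, and 50% is an upper bound.

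There are also real safeguards: sealed envelopes held by an independent statistician, separation of enrolment from list management and assignment, and random choice of one woman per household. They narrow the scope for selection but do not stop inference from visible past allocations.

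The two numerical harms cannot both apply at full size. Under one interleaved list, a recruiter in one district does not directly see the other district's allocations, so certainty falls. Under separate runs by site, certainty is higher but the imbalance is about 1. This stands too.

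On site, the loss is small. A difference of 7 among 101 women costs (7/101)² ≈ 0.5% of within-site information, and a difference of 13 costs about 1.7%. A reader might also make something of 101 per site being odd, but 51 against 50 has no consequence. Per-site lists may be described in a fuller protocol, a site term is often left to the analysis plan, and the allowance for clusters leaves room for one. However, this article does fix a model and a covariate list, and site is in neither.

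On labels, the letters in {21a} may serve only to explain the example sequences, and the iron outcomes are read by blinded laboratory staff. So one cannot say that analyst blinding has failed, only that the wording does not secure it.

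**Conclusion.** The concern holds in a limited form. The clearest defect is the label overlap: analyst blinding is not secured if A and B keep their published meaning, and this needs no assumption about block size. Second, printing an example size and sequences contradicts the stated concealment. The exposure is at most 50% of allocations certain if the examples were the whole scheme, 33% with all six sequences at size 4, and about 6% with sizes 4 and 6 mixed. Third, neither the randomisation nor the stated models and covariates name site, although recruitment is split equally over two districts. The resulting imbalance is modest (SD about 7 women per site) and depends on the assumption of one interleaved list. None of this invalidates the design or affects the sample size of 202. It should be settled before the first envelope is opened.

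**What to change.** Before recruitment starts in December 2025:

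1. Label the analysis dataset with new codes, for example X and Y, assigned independently of the A/B key, and say so in {24b}. Because cookware adherence would reveal the arm under any code, keep it out of the analyst's file until the primary analysis is locked.
2. Have the independent statistician generate a separate list for each site, using all permutations and several block sizes mixed at random. Keep the sizes undisclosed, and remove the example size and sequences from {21a}. Mixed, undisclosed sizes matter more once lists are separate, because each site's team then sees the whole of its own sequence.
3. Add site as a fixed effect to the {27a} models.

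The cost is a regenerated list, a few sentences in an amendment submitted to the ethics committee, and one model term. No additional women or staff are needed. The article is already public, so the old example cannot be withdrawn; the new lists must therefore differ from it.

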### Type of randomization {21b}

Restricted randomization (block randomization) with a 1:1 allocation ratio will be used. The block size and sequence order will remain concealed from the field team to prevent predictability.

### Allocation concealment mechanism {22}

Allocation will be concealed using sequentially numbered, opaque, sealed envelopes (SNOSE), managed exclusively by the independent statistician. Each envelope will contain the allocation code and will be opened only after eligibility confirmation and participant consent.

### Implementation {23}

Field investigators will be responsible for participant enrolment. Randomization and envelope management will be handled by an independent statistician, while intervention allocation will be assigned by a trial coordinator. This separation of responsibilities will ensure that the investigators enrolling participants have no prior knowledge of the sequence.

### Blinding {24}

#### Who will be blinded {24a}

Due to the visible nature of the cookware intervention, participants and field investigators responsible for delivering the intervention cannot be blinded. However, blinding will be maintained for specific trial personnel. Outcome assessors, including laboratory technicians analyzing blood samples for hemoglobin, ferritin, soluble transferrin receptor (sTfR), transferrin saturation, and C-reactive protein (CRP), will remain blinded to group allocation. In addition, data analysts/statisticians will conduct analyses using coded datasets in which group identifiers have been removed, thereby preserving allocation concealment during data analysis.

### How blinding will be achieved {24b}

To maintain blinding, all blood samples will be labelled with anonymized study codes rather than allocation labels. Therefore, the laboratory staff will be unaware of the participants’ group assignments. Similarly, the trial statistician will receive only coded datasets where groups are labelled “Group A” and “Group B.” The cookware used in the intervention arm differed visibly from the control cookware (iron vs. non-iron); hence, participant blinding was not feasible.

### Circumstances for unblinding {24c}

Unblinding of laboratory staff or statisticians is not anticipated. However, if a participant experiences a serious adverse event suspected to be related to the intervention (e.g., severe gastrointestinal symptoms, potential iron overload), the Principal Investigator (PI) may authorize unblinding to confirm group allocation for appropriate clinical management. The procedure will involve the PI contacting the independent statistician who generated the randomization sequence; group assignment will be disclosed only to the treating physician and ethics committee, and not to outcome assessors or data analysts.

### Data collection methods {25}

#### Plans for assessment and collection of outcomes {25a}

Data collection will include both quantitative and qualitative measures to evaluate iron status, dietary intake, adherence, and perceptions of the intervention. Quantitative data will be obtained through structured questionnaires to capture sociodemographic characteristics, health history, and dietary practices, as well as a 24-h dietary recall and Food Frequency Questionnaire (FFQ) to estimate dietary iron intake and food patterns. Laboratory investigations will be carried out at an NABL-accredited laboratory, where trained phlebotomists will collect blood samples for analysis of hemoglobin (Hb), serum ferritin, serum iron, soluble transferrin receptor (sTfR), transferrin saturation (TSAT), total iron binding capacity (TIBC), C-reactive protein (CRP), erythrocyte protoporphyrin, and mean corpuscular volume (MCV). These parameters will be measured at baseline, 6 months, and 12 months, with Hb and ferritin additionally assessed at 3 months. Duplicate testing will be performed on 10% of samples to ensure validity. Qualitative data will be collected through semi-structured interviews and focus group discussions (FGDs) to explore perceptions, facilitators, and barriers to cookware adoption and BCC acceptability, supplemented by field observations recorded during household visits to triangulate adherence and contextual factors. All assessors and laboratory staff will be trained and blinded to group allocation, and standard operating procedures (SOPs) will be followed at all stages to ensure consistency and data quality.

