### Strategies to improve adherence and monitoring {15c}

Adherence will be promoted and monitored through like monthly household visits by field staff to provide reinforcement, troubleshoot issues, and encourage compliance. Food diaries maintained by the participants documented meals prepared using iron cookware. Spot checks during unannounced household visits to observe real-time usage. Structured surveys and interviews to explore barriers and facilitators. Compliance will be defined as use of the provided iron cookware for at least one main meal/day on ≥ 4 days per week, maintained for ≥ 70% of the intervention period. This threshold is based on prior iron-cookware RCTs. Focus group discussions (FGDs) to further refine adherence strategies and address community concerns. Adherence outcomes will be reported, and both per-protocol and intention-to-treat analyses will be performed.

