### Outcomes {16}

The outcome measures and assessment time points are summarized in Table 1. Blood samples will be collected at each time point for the biochemical analysis of iron status markers. Dietary intake and adherence to cookware use will be monitored using structured questionnaires and periodic household visits.

**Table 1 Tab1:** Summary of primary, secondary, and exploratory outcomes with measurement variables, analysis metrics, aggregation methods, and time points (baseline to 12 months)

Outcome type	Measurement variable	Analysis metric	Method of aggregation	Time points
Primary outcome	Serum ferritin (µg/L), CRP-adjusted	Mean change from baseline	Mean ± SD, mean difference (95% CI)	Baseline, 6 months, 12 months
Secondary outcomes	Haemoglobin (g/dL)	Mean change from baseline	Mean difference (95% CI)	Baseline, 6 months, 12 months
	Soluble transferrin receptor (mg/L)	Mean change from baseline	Mean difference (95% CI)	Baseline, 6 months, 12 months
	Transferrin saturation (%)	Mean change from baseline	Mean difference (95% CI)	Baseline, 6 months, 12 months
	Anaemia prevalence (Hb < 12 g/dL, WHO)	Proportion with anaemia	Risk difference, risk ratio (95% CI)	Baseline, 6 months, 12 months
	Nutrition knowledge and practice score	Change in score	Mean difference	Baseline, 6 months, 12 months
	Adherence to iron cookware use (≥ 1 main meal/day, ≥ 4 days/week)	Proportion adherent	Percentage adherence	Monthly monitoring; summarised at 6 months, 12 months
	Adverse events (GI symptoms, iron overload, other harms)	Proportion with ≥ 1 adverse event	Frequency counts, percentages	Ongoing; summarised at 3, 6, and 12 months
Exploratory outcomes	Cost-effectiveness (per unit Hb and ferritin increase)	Incremental cost-effectiveness ratio (ICER)	ICER	6 months, 12 months
	Dietary modifiers (vitamin C intake, tea/coffee, phytates)	Effect modification	Subgroup analyses	Baseline, 6 months, 12 months
	Subgroup analysis by baseline anaemia	Effect difference	Interaction tests	6 months, 12 months
	Community-level adoption of cookware post-trial	Proportion of households continuing usage	Adoption rate (%)	Endline at 12 months; post-trial sustainability follow-up

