#### Ascertainment and frequency

Harms will be assessed systematically at every study contact (baseline, 3, 6, and 12 months) and during monthly home visits in the intervention period, using a structured checklist and open-ended queries. Participants may also self-report harms at any time via a study phone number/WhatsApp. Field workers will document onset, duration, severity, actions taken, and outcome; supervisors verify within 48 h.

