### Plans to promote participant retention and follow-up {25b}

Retention will be promoted through regular household visits, community meetings, and reminder phone calls/WhatsApp messages before scheduled assessments. Monthly home visits will reinforce adherence, troubleshoot problems, and monitor compliance. Compliance will be assessed by Food diaries maintained by participants; Unannounced spot checks by field staff, and Monthly supervisory visits. Compliance is defined as use of the provided iron cookware for ≥ 1 main meal per day on ≥ 4 days per week, sustained for ≥ 70% of the intervention period. Participants not meeting this criterion will be considered non-compliant for per-protocol analysis but will remain in the intention-to-treat (ITT) analysis. Outcome data (Hb, ferritin, and other biomarkers) will be collected for all randomized participants, even if they discontinue or deviate from the intervention, unless consent is withdrawn entirely.

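### The statement that all assessors are blinded cannot hold for cookware adherence and is not credible for field-recorded adverse events; the protocol supports blinding only of laboratory staff and analysts

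*Protocol article*

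**What the plan says.** Section {25a} of the protocol article lists the data sources: structured questionnaires, a 24-hour dietary recall, a food frequency questionnaire, laboratory tests, interviews, focus groups and observations made in households. It closes with a statement that covers them all: "All assessors and laboratory staff will be trained and blinded to group allocation".

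The blinding sections are narrower. Section {24a} says that "participants and field investigators responsible for delivering the intervention cannot be blinded" and that "blinding will be maintained for specific trial personnel". It names laboratory technicians working on blood markers, and data analysts. Section {24b} describes how this is done: coded sample labels for the laboratory and datasets labelled Group A and Group B for the statistician. It adds that "The cookware used in the intervention arm differed visibly from the control cookware (iron vs. non-iron").

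Two of the secondary outcomes in Table 1 are collected outside the laboratory by field staff:

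- **Adherence**, listed as "Adherence to iron cookware use (≥ 1 main meal/day, ≥ 4 days/week"). The adherence section {15c} provides for "Spot checks during unannounced household visits to observe real-time usage". The retention section {25b} lists participant food diaries together with "Unannounced spot checks by field staff, and Monthly supervisory visits".
- **Adverse events**, elicited by checklist and open questions at study contacts and monthly home visits. The section on ascertainment says: "Field workers will document onset, duration, severity, actions taken, and outcome; supervisors verify within 48 h".

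**The concern.** A reader of {25a} would conclude that every outcome in the trial has a blinded assessor. For adherence and adverse events that safeguard is not there.

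Adherence has a wider role than its place in Table 1 suggests. Compliance rates are the third stated objective. The compliance classification also defines the per-protocol set in {27b}, and {27c} uses the per-protocol analysis to test robustness. If staff who have been encouraging pot use also judge whether the pots are used, the classification may be generous. Both the compliance result and the membership of the per-protocol set would then shift.

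For adverse events, what is at stake is the comparison of symptom counts and severity between arms, which depends on how the questions are put and how often.

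**Working it through.** No arithmetic beyond a count applies. The check sets the sections of the protocol article side by side.

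**1. What blinding is actually described?** Section {24b} gives two mechanisms: coded tubes and coded datasets. No section describes a mechanism for anyone who meets the participant. Section {24a} introduces its outcome assessors through laboratory technicians, but as examples, so it does not expressly exclude other assessors. The unqualified statement in {25a} fills that gap with a claim that has no mechanism behind it.

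**2. Adherence.** The thing measured is use of the iron cookware that was supplied. Iron cookware is supplied only to the intervention arm; under the trial design section {12}, controls keep their usual utensils. Anyone who observes the measure therefore learns the allocation. The observers are field staff ({25b}). The BCC section describes monthly home visits that both reinforce the messages and monitor cookware use, and {15c} says the monthly visits encourage compliance. Blinding is impossible here, and promotion and monitoring share a visit.

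**3. Adverse events.** Field workers record symptoms and severity from women who know their arm, partly in homes where the cookware is in use. The BCC section describes monthly individual visits for the intervention group only, and the harms section does not say whether control women are also visited monthly. How intensively events are sought may therefore differ by arm as well. The exception is iron overload judged on ferritin and transferrin saturation, which the laboratory measures on coded samples.

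**4. Knowledge and practice score.** The article does not say who administers the questionnaire or where. The blinding claim is neither supported nor contradicted for this outcome.

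**5. Count over Table 1.**

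| Outcome | Basis | Assessor blinding as described |
|---|---|---|
| Ferritin (primary) | laboratory | supported |
| Haemoglobin, sTfR, transferrin saturation, anaemia prevalence | laboratory | supported |
| Adherence | observation and diaries | impossible |
| Adverse events | field record, with a laboratory part for iron overload | not credible, except the laboratory part |
| Knowledge and practice score | questionnaire | not specified |

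The secondary outcomes add up as 4 supported + 2 affected + 1 unspecified = 7.

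**The case against.** The best reply is that {24a} is the governing section on blinding and already concedes that delivery staff are unblinded. The discussion also lists participant unblinding and inaccurate self-report as limitations. On that view {25a} contains one over-broad sentence. This is partly right, and it keeps the correction small. But {25a} is where the protocol says how outcomes are assessed, and the discussion does not mention unblinded assessors.

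A second reply is that checks already exist. Under {29} an internal monitoring team that includes field supervisors makes monthly household spot checks, supervisors verify adverse event records, and the study physician assigns causality. That stands: adherence is not left solely to the staff who counsel. These checks are not blinded either, so they do not make the statement true.

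A third reply is that compliance is in substance a description of the intervention arm, so blinding to allocation has little meaning for it. That is fair. The concern is then the observer's interest rather than knowledge of the arm, and it is a further reason not to claim blinding.

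Three stronger readings are tempting, and the documents do not support them:

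- A reader might infer that all these outcomes are biased in favour of the intervention. For adverse events the direction is uncertain: closer contact and prompting for expected symptoms could raise counts in the intervention arm.
- A reader might infer that BCC staff will score the knowledge questionnaire. The article is silent on this, and a separate interviewer is not ruled out.
- A reader might want an inflated false-positive rate for the score. The documents give no bias size, and part of any bias would come from respondents giving the taught answer, which assessor blinding would not remove.

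**Conclusion.** The statement in {25a} is wrong as written. It is untrue for adherence, not credible for field-recorded adverse events, and at odds with {24a} and {24b}. Two of seven secondary outcomes are affected, together with the compliance objective and the make-up of the per-protocol set. The primary outcome and the four laboratory-based secondary outcomes are safe, as is the laboratory part of iron overload.

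The conclusion on adherence needs no assumption, because the measure itself reveals the arm. The conclusion on adverse events assumes that the field workers who record them are those who visit the homes, as the ascertainment section implies, and that no separate blinded assessor exists, since none is described. The size of any bias cannot be derived from the document.

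**What to change.** - **Wording.** In {24a} and {25a}, limit the blinding claim to laboratory markers and coded-data analysis. State that adherence and participant-reported adverse events are assessed unblinded, and that the direction of any bias in adverse events is uncertain.
- **Compliance classification.** For the third objective and the per-protocol set, take observed use from the spot checks that the supervisors or monitoring team already make under {29}, or from field staff who did not counsel that woman. Food diaries still supply the day-by-day count that the definition needs.
- **Questionnaires.** Have the knowledge and practice questionnaire and the dietary questionnaires given in the same way in both arms, by existing staff who did not deliver BCC to that woman, and say so.

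None of this changes the sample size, the primary outcome or the intervention. The cost is an edit to two sections and some scheduling effort; staffing numbers are not given, so the effort cannot be sized. Adherence figures may look less favourable. The staffing changes separate promotion from measurement but do not make these outcomes blinded, so the wording change is needed in any case.
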